# Abstract

**Background** Worldwide, lesbian, gay, bisexual, transgender and intersex (LGBTI) people contend with high risks for HIV infection, stigma and discrimination, and for exclusion from HIV and other health services. In many low- and middle-income countries, LGBTI people are often hidden, marginalised and difficult to assess as part of general population-based surveys. Thus, assessing their exposures and outcomes and burden of HIV disease is extremely challenging. This presents a dilemma for HIV surveillance as their omission from surveillance systems leaves significant gaps in our understanding of HIV epidemics.

**Objective** This research project is aimed at conducting an observational, non-interventional, global cross-sectional internet survey in LGBTI participants to examine how various demographic, economic, socioecological, homophobic, psychosocial, attitudinal and behavioural variables potentiate HIV risk behaviour. We likewise aim to examine self-reported HIV prevalence, exposure to HIV related stigma and discrimination, and to study the association between these socioecological parameters and HIV care and treatment coverage in the survey participants.

**Methods** We imply internet sampling method to conduct the cross-sectional survey recruiting consenting adult LGBTI participants. We select internet sampling for it demonstrated to be particularly useful for hard-to-sample populations, higher number of respondents among hard-to-reach populations, faster recruitment, lower operational cost, greater level of anonymity and security provided to participants. Acknowledging selection bias, we may apply techniques, e.g. prediction modelling, to correct for the bias that results from differential access to, and use of, the internet. To safeguard the data privacy, rights and welfare of the research participants, the access to the online survey will be provided via anonymous weblink. The survey will be opened for three (3) months. Our cross-sectional study is observational by nature and it does not alter the exposure status of the consenting respondents and thus warrants minimal to no risk for the participants. We will examine the outcome and the exposures in the target population and will study their association. Our survey questionnaire provides essential components to fulfil the above objective and was developed using selected standard protocols.

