## Methods and Design

### a) The scientific design of the study

#### *The survey objectives*

This research project is aimed to:

- conduct a cross-sectional observational, non-interventional, internet survey in consenting 18+ year-old LGBTI participants using an anonymous web-based self-administered questionnaire without any geographical restrictions;
- examine correlates of HIV infection to understand how survey variables, such as demographic, economic, socioecological, homophobic, psychosocial, attitudinal and behavioural, potentiate HIV risk behaviour and access to and uptake of HIV care and treatment services;
- provide evidence in favour of more LGBTI-inclusive health and HIV service delivery, advocacy, and policymaking.

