### Module 3: HIV-related stigma and discrimination

If you are HIV-positive, you may face stigma. Let's talk about it

Choose how you feel about each statement. We understand some questions might sound disturbing. Please share your experience. It will help to create a more inclusive environment for everyone

An exit button is always available at the beginning of each module. Respondent can always scroll back to it

☐ OK (click is required)

62. I am not as comfortable as I used to be in dating since I learned I have HIV

- ☐ strongly agree
- ☐ agree
- ☐ disagree
- ☐ strongly disagree
- ☐ I don't know

63. I disclosed my HIV status on my online profile in the main app I'm using

- ☐ yes
- ☐ no

64. If no, is there any reason you don't mention your HIV status? (tick as many as apply)

- ☐ I revealed it before and couldn't meet anybody
- ☐ I'm afraid of rejection
- ☐ I say I am looking for safe sex (like with a condom) and I do not need to tell them my HIV+ status
- ☐ I don't need to mention it
- ☐ I'm undetectable
- ☐ I don't want to mention it
- ☐ other
- ☐ does not apply to me (I disclosed my HIV+ status on my profile)

65. I changed the way I have sex since I know I'm HIV positive

- ☐ yes
- ☐ no
- ☐ I don't know
- ☐ does not apply

66. Since I've known that I'm HIV-positive, I have sex with:

- ☐ people regardless of their HIV status
- ☐ only HIV-positive partners
- ☐ I don't have sex anymore
- ☐ does not apply

67. Some people avoid touching me once they know I have HIV

- ☐ strongly agree
- ☐ agree
- ☐ disagree
- ☐ strongly disagree
- ☐ I don't know

68. People I care about stopped contacting me after learning I have HIV

- ☐ strongly agree
- ☐ agree
- ☐ disagree
- ☐ strongly disagree
- ☐ I don't know

69. I have lost friends by telling them I have HIV

- ☐ strongly agree
- ☐ agree
- ☐ disagree
- ☐ strongly disagree
- ☐ I don't know

70. Telling someone I have HIV is risky

- ☐ strongly agree
- ☐ agree
- ☐ disagree
- ☐ strongly disagree
- ☐ I don't know

71. I work hard to keep my HIV a secret

- ☐ strongly agree
- ☐ agree
- ☐ disagree
- ☐ strongly disagree
- ☐ I don't know

72. I am very careful whom I tell that I have HIV

- ☐ strongly agree
- ☐ agree
- ☐ disagree
- ☐ strongly disagree
- ☐ I don't know

73. People with HIV are treated like outcasts

- ☐ strongly agree
- ☐ agree
- ☐ disagree
- ☐ strongly disagree
- ☐ I don't know

74. Most people believe a person who has HIV is dirty

- ☐ strongly agree

- ☐ agree
- ☐ disagree
- ☐ strongly disagree

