- ☐ I don't know

75. Most people are uncomfortable around someone with HIV

- ☐ strongly agree
- ☐ agree
- ☐ disagree
- ☐ strongly disagree
- ☐ I don't know

76. I feel guilty because I have HIV

- ☐ strongly agree
- ☐ agree
- ☐ disagree
- ☐ strongly disagree
- ☐ I don't know

77. People's attitudes about HIV make me feel worse about myself

- ☐ strongly agree
- ☐ agree
- ☐ disagree
- ☐ strongly disagree
- ☐ I don't know

78. I feel I'm not as good a person as others because I have HIV

- ☐ strongly agree
- ☐ agree
- ☐ disagree
- ☐ strongly disagree
- ☐ I don't know

79. In the last 12 months, have you ever been excluded from social gatherings or activities (e.g., weddings, funerals, parties, clubs) because of your HIV status?

- ☐ yes, once
- ☐ yes, several times
- ☐ no
- ☐ I don't know
- ☐ it doesn't apply to me

80. Are you currently taking HIV (antiretroviral) treatment? (choose one)

- ☐ yes
- ☐ no, medication is not available at the clinic or pharmacy
- ☐ no, medication is not affordable for me
- ☐ no, I am unable to collect medications at the clinic or pharmacy
- ☐ no, I cannot tolerate medication side effects or am worried about taking the pills
- ☐ no, I do not feel treatment is needed
- ☐ no, I am worried someone would find out my HIV status
- ☐ no, I am not ready to deal with my HIV infection
- ☐ no, I am worried the healthcare workers would treat me badly or disclose my HIV status without my consent
- ☐ no, I do not qualify for treatment in my country because my CD4s are too high
- ☐ no, for other reasons

81. In the last 12 months, have you been told you have an undetectable viral load or are virally suppressed (“good viral load”)?

- ☐ yes
- ☐ no, I have not had a viral load test in the last 12 months
- ☐ no, I had a viral load test and am waiting for the results
- ☐ no, the virus was detectable/I am not virally suppressed
- ☐ I don't know what viral load or viral suppression are
- ☐ I don't have treatment

82. Living with HIV can open new horizons and positively affects us deep inside. Which of the following have been positively affected by your HIV status (tick as many as apply)

- ☐ My self confidence
- ☐ My self-respect
- ☐ My ability to respect others
- ☐ My ability to cope with stress
- ☐ My ability to better take care of my health
- ☐ My ability to contribute to my community
- ☐ Other
- ☐ None of the above

- ☐ PREV (*clicking here brings the respondent to earlier module in case she/he would like to change*)

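### Module 3 does not record time since HIV diagnosis, so the stated association of HIV stigma with treatment coverage is open to confounding that cannot be fully adjusted for later

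*Protocol*

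**What the plan says.** The Abstract states the aim, directly after naming HIV-related stigma: "to study the association between these socioecological parameters and HIV care and treatment coverage in the survey participants". The survey objectives in section a) repeat it, asking how survey variables "potentiate HIV risk behaviour and access to and uptake of HIV care and treatment services".

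For HIV-positive respondents the data come from Module 3 of Appendix 1:

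- **Exposure without a recall window.** Q67: "Some people avoid touching me once they know I have HIV". Q68: "People I care about stopped contacting me after learning I have HIV". Q69: "I have lost friends by telling them I have HIV".
- **Exposure with a window.** Q79, on exclusion from social gatherings, is limited to the last 12 months.
- **Outcomes.** Q80 asks about current treatment ("Are you currently taking HIV (antiretroviral) treatment? (choose one"). Q81 begins "In the last 12 months, have you been told you have an undetectable viral load or are virally suppressed".

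Q66 opens with "Since I've known that I'm HIV-positive, I have sex with", and Q62 and Q65 are also anchored to learning of the infection. The length of that period is not asked there or anywhere else in Q2 to Q82. Q61, which routes people to Module 3, asks for HIV status only. Q29 in Module 1 dates the last HIV test in bands that stop at more than 12 months ago. Section p), on limitations, does not mention the gap.

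**The concern.** Q68 and Q69 describe past events over an open period. Someone diagnosed ten years ago has had more opportunity for such losses than someone diagnosed last month. The longer-diagnosed person has also had more time to start treatment and to be told of a suppressed viral load. Time since diagnosis is therefore a plausible common cause of exposure and outcome. If it is ignored, a harmful association of stigma with treatment can be pulled towards no association.

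This cannot be left to a later analysis plan, because the protocol fixes the questionnaire. Respondents are not tracked between rounds (section a, on timing and intervals), and section o) says they cannot be contacted individually after completion. At stake is the reading of whether, and how strongly, HIV stigma goes with lower treatment coverage, which the sponsor wants to use for advocacy and programme design.

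**Working it through.** **The plan's own figure.** The protocol gives no rate or effect size for this association. Its only computed design figure is N = 116 in the sample-size section (five predictors, f² = 0.15, power 0.90, alpha 0.05). With the noncentral F test, u = 5, v = N − u − 1 and λ = f²N, N = 116 gives power 0.902, so the figure reproduces. It is not in dispute and serves below only to cost the fix.

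**Assumed inputs.** All are assumptions.

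- Time since diagnosis <1, 1–5, >5 years: 15%, 35%, 50%.
- Agreement with Q69 by band: steep 10/30/50%, mild 20/30/40%, or falling with time 60/45/30%.
- On treatment among those not reporting the loss: 65/88/95%. Suppressed: 45/80/90%.
- True odds ratio within each band: 0.60.

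**Formula.** For weight w, agreement s and treated proportion p in each band, the treated proportion among those agreeing is e = 0.6·o/(1 + 0.6·o), with o = p/(1 − p). The crude proportions are Σws·e/Σws and Σw(1 − s)·p/Σw(1 − s).

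**Steep case, treatment.**

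- e = 0.527, 0.815, 0.919.
- Agreeing: weights 0.015, 0.105, 0.250 (sum 0.370); treated 0.3233/0.370 = 0.874.
- Not agreeing: weights 0.135, 0.245, 0.250 (sum 0.630); treated 0.5409/0.630 = 0.858.
- Crude odds ratio = (0.874/0.126)/(0.858/0.142), which is 1.14 from unrounded values.

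**Other cases by the same steps.**

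| Case | True OR | Crude OR |
|---|---|---|
| Steep, treatment | 0.60 | 1.14 |
| Steep, suppression | 0.60 | 1.12 |
| Mild, treatment | 0.60 | 0.86 |
| Falling, treatment | 0.60 | 0.43 |
| Steep, treatment, no true effect | 1.00 | 1.85 |
| Steep, treatment, bands 5/35/60% | 0.60 | 0.90 |
| Mild, treatment, bands 5/35/60% | 0.60 | 0.75 |

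**Second model.** Two bands (diagnosed within a year or longer ago) and a true odds ratio of 0.70 give crude values of 0.72, 0.80, 0.98, 1.32 and 1.85. The recently diagnosed share rises from 5% to 30% and the contrasts widen across these five scenarios.

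**Q29 as an adjustment variable.** Take the 20% scenario of the second model (agreement 15% against 50%, treatment 65% against 93%, true 0.70). The Mantel-Haenszel odds ratio stratified by Q29 is 0.70 if no long-diagnosed respondent reports a test within 12 months, 1.04 if 20% do, and 1.18 if 40% do.

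**Q29 as a restriction.** A diagnosis cannot be later than the last HIV test, so a positive respondent last tested more than 12 months ago was diagnosed more than 12 months ago. Dropping the <1-year band from the three-band model, a true 0.60 shows as 0.74 (steep), 0.67 (mild) or 0.52 (falling) for treatment, and 0.72 for suppression (steep). The sample kept is 0.85 × 0.80 = 68% if 20% of the long-diagnosed report a recent test, and 0.85 × 0.60 = 51% if 40% do.

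**The case against.** The strongest reply is that the restriction on Q29 already brings the steep case from 1.14 to 0.74. That stands, and a claim that no model can deal with the problem would be wrong. It is still a partial remedy. It loses sample, cannot separate 1–5 from more than 5 years, and assumes that the Q29 answer is unrelated to stigma and treatment within a duration band.

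Other parts of the reply also stand:

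- **Reversal.** A reader might infer that the association will change sign. The documents give no rates, and the milder inputs show attenuation only. The figures are also crude odds ratios, whereas the protocol plans multiple regression.
- **Q80 for the newly diagnosed.** A reader might infer that no answer fits them. The list includes not being ready to deal with the infection and other reasons, and Q81 allows for a pending result.
- **Other evidence on stigma.** Q79 is limited to 12 months, and Q80 offers fear of discovery and of poor treatment by healthcare workers as reasons for not being treated. Neither depends on counting losses over years.
- **Scope.** Accumulation concerns Q68 and Q69, and arguably Q67, which is in the present tense. How present feelings (Q76 to Q78) move with time is conjecture. The two research questions listed first in the data analysis section do not need this variable.

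The questionnaire principles also ask for brevity. One closed item on a standard confounder, shown only to HIV-positive respondents, hardly conflicts with that.

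**Conclusion.** The point holds as a measurement gap affecting one stated aim. Time since diagnosis is not collected, it plausibly drives both the open-ended enacted-stigma items and Q80 and Q81, and it cannot be recovered later. With a true odds ratio of 0.60 for treatment, the crude value runs from 0.43 to 1.14 over the assumed inputs. If losses accumulate, movement towards 1 is the likelier outcome. An apparent benefit appears only with a sizeable recently diagnosed share (about 15–20% or more in these models) and strong contrasts between bands. If agreement instead falls with time, the association is exaggerated. The direction and size rest entirely on assumed rates; the absence of the variable and the open recall period rest on the questionnaire itself. This is worth correcting because the correction is cheap. It does not invalidate the survey.

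**What to change.** Add one item at the start of Module 3: *When did you first learn you have HIV? Less than 1 year / 1–5 years / more than 5 years.* Adjust for it, or stratify by it, in every model relating the HIV-stigma items to Q80 and Q81. Report Q81 separately for people diagnosed less than 12 months ago, for whom its window is incomplete.

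If the questionnaire can no longer change, name the gap in section p) and add the restriction to those last tested more than 12 months ago as a sensitivity analysis.

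The cost is one extra closed question for HIV-positive respondents, its translations and a slightly longer questionnaire. Broad bands keep the added disclosure risk small. On the protocol's own sample-size basis (f² = 0.15, power 0.90, alpha 0.05), N rises from 116 to 123 if the bands enter as one linear score (six predictors), or to 130 as two indicators (seven predictors). These totals are only indicative, since they refer to the overall test in a linear regression and treatment status is binary.

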  - currently on antiretroviral therapy

- discussed pre-exposure prophylaxis
- use of pre-exposure prophylaxis
- health-care stigma

The consensus questionnaire (see [appendix 1](#)) consists of three modules:

- 1st module for LGBTI people, comprising 45 questions;
- 2nd module for MSM and transgender people, comprising 15 questions;
- 3rd module on HIV stigma, comprising 22 questions.

It was our preference to start and finish the survey with relatively comforting questions and statements to reduce any unforeseen discomfort in the participants.

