#### c) Sampling strategy, recruitment and voluntary informed consent

The target population of the survey are 18+ year-old LGBTI people. The survey can be accessed using a web [link](#) that will be provided at LGBTI social networks, e.g. the LGBT Foundation social networks, as well as national and regional LGBTI community networks. The survey will be opened for a duration of 3 months. Recruitment will not involve any direct recruitment and is anonymized. Participation in the survey is not incentivised. We are aware of the limitations associated to these voluntary recruitment channels and we are exploring, with LGBTI civil society organisations and UNAIDS teams at country and regional levels, all additional opportunities that could increase the participation of marginalised or remote communities and individuals.

It was considered that participants who are afraid to share information about risk behaviours or HIV status may drop out of the survey or falsify their responses. To successfully survey LGBTI people, these biases are being minimized by obtaining fully informed voluntary consent at the start of the survey from participants and ensuring their absolute confidentiality.

The informed consent of voluntary participants is summarised at the introduction of the survey and the following information is provided through a link:

- a concise description of the survey and the organization conducting it, the survey objectives, the populations being invited to participate;
- a clear indication that participation is voluntary and that participants have the right of withdrawal from the survey at any time, or skip any sensitive question/s;
- a description of the participant's role in the survey, including duration of participation, the general nature of the questions;
- a description of the possible discomforts of participation;
- a description of the benefits to the community that are expected to come from the survey
- a description of how the findings will be made available to the respondents and the LGBTI community
- measures made to protect the privacy and confidentiality of the participant and any information that the person provides;
- documentation that the protocol was reviewed and approved by Research Ethics Review Committee (*to be completed once WHO ERC approval*);
- how the results of the survey will be used. This includes explicitly the possible use of the data for scholar purpose, such as doctoral or post-doctoral productions by the research team

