### Exclusion and Non-qualifiers

The online questionnaire is built in three modules: A socioecological module; a module specific for men having sex with other men; and a module on HIV. Respondents must complete a module and click on 'next' in order to have her/his responses recorded. Any respondent leaving the survey before completing a module is *de facto* excluded from the survey. Respondent choosing to click on the 'exit' button are also excluded from the survey.

To increase the quality of the dataset, the research team will construct discrepancy flags which indicate whether respondents had supplied inconsistent data in different areas.

Non-qualifiers are respondents who did not meet the criteria for inclusion in the study. Non-qualifying cases include:

- Consent not provided
- Not providing a numeric value for age
- Not providing an age of 18 or higher
- Not belonging to any LGBTI groups

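### Q80 and Q81, the only direct treatment and viral load items, are kept only for respondents who submit all of module 3, so treatment coverage and its associations may be biased by selective completion

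*Protocol*

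**What the plan says.** The Abstract states an aim to "study the association between these socioecological parameters and HIV care and treatment coverage in the survey participants". The survey objectives in section a) likewise include access to and uptake of HIV care and treatment.

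Current treatment is asked at Q80, "Are you currently taking HIV (antiretroviral) treatment? (choose one", and viral suppression at Q81. Both stand near the end of module 3 (Appendix 1). That module is offered only to respondents who report being HIV-positive at Q61, and its opening text says: "We understand some questions might sound disturbing".

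The recording rule is in section l), under Exclusion and Non-qualifiers: "Respondents must complete a module and click on 'next' in order to have her/his responses recorded". Leaving part-way is covered by the sentence beginning "Any respondent leaving the survey before completing a module is", which makes such a person excluded de facto. The rule adds: "Respondent choosing to click on the 'exit' button are also excluded from the survey".

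Section c) recognises that "participants who are afraid to share information about risk behaviours or HIV status may drop out of the survey or falsify their responses", and also lets respondents skip sensitive items. Section l) allows multiple imputation and promises a count of people who did not complete the survey.

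**The concern.** The outcome sits behind a block of sensitive items and is kept only if the whole block is submitted. Someone who has already reported being HIV-positive but stops at, say, Q74 contributes nothing on treatment or suppression. Whether the outcome is observed may then depend on stigma, on treatment status, or on both.

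Such dependence is plausible from the protocol's own content. Several of Q80's reasons for not being treated concern fear of discovery, unreadiness to deal with the infection, or expected bad treatment by health workers. The background section reports lower adherence to treatment among people facing enacted stigma. Section g) names one module 3 statement that precedes Q80 (Q69, on losing friends) as a possible trigger of anxiety.

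At stake are the reported coverage and suppression percentages and every association with them. That includes associations with module 1-2 variables, because treatment is recorded nowhere else.

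**Working it through.** **Item count.** Section a), Questionnaire development, describes a "module on HIV stigma, comprising 22 questions".
- Counting from Q61: 82 - 61 + 1 = 22, which reproduces the stated figure. It also agrees with 45 + 15 = 60 items in modules 1 and 2.
- Printed under the module 3 heading are Q62-82: 82 - 62 + 1 = 21.
- Items printed before Q80: 80 - 62 = 18. Q80 and Q81 are the 19th and 20th of those 21.
- Not all 18 measure stigma. Q63, Q65 and Q66 ask about profile disclosure and sexual behaviour, and Q64 asks the reasons for not disclosing.
- Q64 has an option on being undetectable, but only as a reason for not disclosing. It does not measure suppression.

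**What is lost on stopping mid-module.** The rule can be read in two ways.
- Only the unfinished module is dropped: Q1-61 remain, but Q62-81 are all missing for that person.
- The person is removed from the survey altogether: Q61 and every predictor go too, and the number of HIV-positive respondents who stopped cannot be seen in the data.

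Q80-81 are lost under both readings.

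**What selective completion can do.** The documents give no completion rates, so every rate here is assumed. Let half the HIV-positive respondents have high stigma, with true treatment coverage 90% at low and 75% at high stigma.
- True overall coverage: (0.90 + 0.75)/2 = 82.5%.
- True odds ratio (OR), high versus low: (0.75/0.25)/(0.90/0.10) = 3/9 = 0.33.

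Let c be the probability of completing module 3 in each cell (H/L = high/low stigma, T/U = treated/untreated). Then

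observed OR = true OR × (c_HT × c_LU)/(c_HU × c_LT).

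Completion is 90% except where the table says otherwise.

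| Who completes at 60% | Odds, low | Odds, high | Observed OR | Coverage, low / high | Overall coverage |
|---|---|---|---|---|---|
| All high-stigma | 0.81/0.09 = 9 | 0.45/0.15 = 3 | 0.33 | 90% / 75% | 1.26/1.50 = 84.0% |
| All untreated | 0.81/0.06 = 13.5 | 0.675/0.15 = 4.5 | 0.33 | 93.1% / 81.8% | 1.485/1.695 = 87.6% |
| Untreated high-stigma only | 9 | 0.675/0.15 = 4.5 | 0.50 | 90% / 81.8% | 1.485/1.725 = 86.1% |
| Treated high-stigma only | 9 | 0.45/0.225 = 2 | 0.22 | 90% / 66.7% | 1.26/1.575 = 80.0% |

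Overall coverage moves in every row, up in three and down in one. The OR moves only when stigma and treatment act jointly on completion, and then in either direction. In the second row the OR is unchanged, but the difference in coverage shrinks from 15 points to 93.1 - 81.8 = 11.3.

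A stronger joint pattern, also assumed, takes true coverage of 86% and 74%. Completion is 90% in both low-stigma cells, 70% in treated high-stigma and 40% in untreated high-stigma respondents. The OR goes from 0.46 to 0.46 × (0.70 × 0.90)/(0.40 × 0.90) = 0.81, and overall coverage from 80.0% to 84.9%.

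**The case against.** A reader might infer that coverage is necessarily overstated and the stigma-treatment association pulled toward the null. The documents do not support that. Loss that depends on stigma alone leaves the association intact, equal loss among the untreated in both groups leaves the OR intact, and loss among treated high-stigma respondents moves it away from the null and lowers coverage. This part of the objection stands in full.

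A reader might also say that only people who can endure the stigma items are measured. That is too strong. Sensitive items may be skipped, so a respondent can pass over them, answer Q80-81 and submit. This reduces the loss but does not remove it, because the module must still be submitted.

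Section a), Data management, reports a small online test that looked for drop-off at particular points and went adequately, and pre-testing led to modules and questions being re-ordered. No result is given for HIV-positive respondents or for module 3, so this is reassuring only in general terms.

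Multiple imputation has something to work with if modules 1 and 2 are kept: Q9, Q26-32, Q51 and Q54-60 cover openness, stigma, avoidance of care and attitudes. It still has to model the outcome and the module 3 stigma answers together, and it cannot test whether the untreated are the ones who stop. The promised count of non-completers shows how many were lost, not who they were.

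Finally, moving Q80-81 does not rescue the association with Q62-79, since those exposures remain in the all-or-nothing module. This is correct and limits what the change can achieve.

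**Conclusion.** The structural point follows from the text alone. The only direct treatment and suppression items come after 18 others in an optional module that is kept only if completed, so coverage and all its associations are conditional on submitting module 3. Question order and the recording rule are fixed in this protocol, and no later analysis recovers answers that were not recorded.

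That bias results is possible and plausible, but not demonstrated. Its size and direction cannot be derived from the documents. In the four assumed scenarios with a true OR of 0.33, the observed OR ran from 0.22 to 0.50, and overall coverage from 80.0% to 87.6% against a true 82.5%. These figures depend entirely on the assumed completion rates and on the assumed half-and-half split by stigma.

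**What to change.** - Place Q80 and Q81 directly after Q61, shown only to those answering HIV-positive there, and save them with Q61 as a submitted page before Q62 appears.
- Amend the exclusion rule in section l) so that leaving or exiting module 3 does not delete pages already submitted. Without this, the reordering could be undone by the rule itself. Say the same in the consent information, and keep the withdrawal route in section k).
- Report coverage and suppression among all respondents HIV-positive at Q61, stating how many answered each item.
- Report the fraction of Q61-positive respondents who completed module 3, and compare completers with non-completers on module 1-2 variables.
- Report any association of treatment with Q62-79 as resting on module 3 finishers, with that limitation stated.

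The cost is moving two existing questions, one skip rule and one page save in every language version, plus the change to the exclusion text. No question is added. The downside is that HIV-positive respondents who decline module 3 see two more items and do not end on the positive closing item Q82, which departs for them from the stated preference for a comforting finish. The change has to be made before the survey opens.
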